## Abstract

**Introduction:**

Sexually transmitted infections (STIs) can cause serious morbidity, including pelvic inflammatory disease, and adverse pregnancy outcomes. In low/middle-income countries, limited laboratory infrastructure has resulted in a syndrome-based approach being used for management of STIs, which has poor sensitivity and specificity, leading to considerable underdiagnosis and overtreatment. The WHO has called for development and evaluation of strategies to inform replacement of syndromic management by diagnostic testing.

The aim of this project is to evaluate a strategy of point-of-care testing for six STIs in antenatal care (ANC) in Zimbabwe.

**Methods and analysis:**

A prospective interventional study will be conducted in ANC clinics in Harare province, Zimbabwe. One thousand pregnant women will be recruited when registering for routine ANC. Alongside routine HIV and syphilis testing, participants will be offered an integrated screening package including testing for *Chlamydia trachomatis* (CT), *Neisseria gonorrhoeae* (NG), *Trichomonas vaginalis* (TV) and hepatitis B. All individuals with STIs will receive treatment, partner notification services, risk reduction counselling and referral if needed according to national guidelines. Gonorrhoea samples will be cultured and tested for antimicrobial resistance as per WHO enhanced gonococcal antimicrobial surveillance programme guidelines.

The primary outcome measure is the composite prevalence of CT, NG, TV, syphilis and hepatitis B. A mixed-methods process evaluation and economic evaluation will be conducted to understand the acceptability, feasibility and cost-effectiveness of integrated STI testing, compared with standard of care (syndromic management).

**Ethics and dissemination:**

The study protocol was approved by the Medical Research Council of Zimbabwe, the Biomedical Research and Training Institute Institutional Review Board, and the London School of Hygiene & Tropical Medicine Research Ethics Committee. Results will be submitted to open-access peer-reviewed journals, presented at academic meetings and shared with participating communities and with national and international policymaking bodies.

**Trial registration number:**

NCT05541081

STRENGTHS AND LIMITATIONS OF THIS STUDYThe mixed-methods approach, with qualitative and quantitative data, will allow for the development of a multilayered understanding of the acceptability and feasibility of this integrated screening package.Inclusion of an economic evaluation will allow for estimation of the cost-effectiveness of this screening package compared with routine care, which is essential for considering the scalability and sustainability of the programme.The large sample size will ensure an estimation of sexually transmitted infection (STI) prevalence with high precision among antenatal attendees in Harare.This study does not include a formal outcome evaluation to assess the impact of this integrated screening package for STIs on adverse birth outcomes, which will need to be informed by future studies.Our focus on urban clinics will likely limit the generalisability of our findings to other urban centres in Southern Africa.

## Introduction

Globally, there were an estimated 374 million infections of *Chlamydia trachomatis* (CT), *Neisseria gonorrhoeae* (NG), *Trichomonas vaginalis* (TV) and syphilis in 2020 among people aged 15–49 years.^1^ Untreated sexually transmitted infections (STIs) can cause adverse pregnancy outcomes, congenital infection and pelvic inflammatory disease.^2^ STIs are also associated with increased risk of both HIV transmission and acquisition.^3^

There are multiple contributing factors to the persistence of the high incidence of STIs globally. Complex sociocultural barriers such as stigma, limited sexual health education and barriers to condom use, and biomedical factors such as asymptomatic infections and increasing levels of antimicrobial resistance (AMR) have been exacerbated in recent years by a substandard global response to STIs, characterised by a lack of funding and political commitment.^1^

Effective management of STIs in low/middle-income countries (LMICs) is additionally hindered by the use of syndromic management, which is the provision of treatment to an individual presenting with symptoms and/or signs that may be caused by an STI.^4^ This is problematic as the majority of curable STIs are asymptomatic, particularly in women, and are missed by syndromic management.^5^ Furthermore, treatment for infections that patients may not have may lead to side effects and increased AMR.^6^

Diagnostic platforms that do not require complicated laboratory infrastructure are available, but cost and lack of evidence on how they should be implemented to maximise both clinical effectiveness and cost-effectiveness in LMICs limit their implementation. Integration of diagnostic STI testing into health systems is likely to be key to reducing rates of STIs in LMICs, and the WHO has called for evidence to inform replacement of syndromic management by diagnostic testing.^7 8^

A group that may particularly benefit from the introduction of diagnostic testing for STIs is pregnant women. Pregnant women in LMICs are a high-risk population for STIs,^9^ and diagnosis and treatment may prevent adverse pregnancy outcomes and congenital transmission of some infections.^10^ As point-of-care (POC) testing for HIV and syphilis has already been integrated into antenatal care (ANC) services, this provides a platform for further STI testing and management and potentially enhances operational feasibility. In addition to curable STIs, this is also pertinent for hepatitis B, as testing is noted to be essential for the WHO’s triple elimination initiative, which aims to eliminate vertical transmission of HIV, syphilis and hepatitis B.^11^ Key to triple elimination is the provision of a multidisciplinary approach within routine ANC services.

There are limited data on STI prevalence among pregnant women in Zimbabwe. Prevalence of CT up to 26.0%, of NG up to 6.4% and TV up to 24.8% has been reported in pregnant women in South Africa and Zambia.^12–16^ A 2010 study found a TV prevalence of 11.8% and syphilis prevalence of 1.2% among pregnant women in Harare.^17^ Recent studies among female youth in Harare have demonstrated a combined CT/NG prevalence between 18.2% and 19.5%.^18 19^ A prevalence of hepatitis B ranging between 3.1% and 5.3% has been reported in pregnant women in South Africa.^20–22^

Control of STIs, particularly NG, is additionally compromised by AMR.^23^ Surveillance is key to identifying and monitoring AMR. WHO and the Centers for Disease Control, USA established the Enhanced Global Gonococcal Antimicrobial Surveillance Programme (EGASP) in 2015.^24^ A sample of at least 100 gonococcal isolates per year per country is recommended.^23^ However, gonococcal AMR data are still extremely limited and in 2018, only 5 of 47 countries in the WHO African Region reported susceptibility testing for NG of at least one of ceftriaxone, cefixime, ciprofloxacin and azithromycin.^25–28^

### Rationale

Evidence is required to inform the use of diagnostic testing for STIs in LMICs, at both national and international levels, particularly regarding acceptability, feasibility and cost-effectiveness. Additionally, there is a data gap regarding the prevalence of STIs among pregnant women in Zimbabwe. Given the paucity of data on AMR in NG in Africa, there is also a need to strengthen AMR surveillance systems.

### Aims and objectives

The overall aims of this study are to implement and evaluate a strategy for integration of POC diagnostics for STIs into ANC settings and to establish a gonococcal AMR surveillance strategy aligned with EGASP in Zimbabwe.

The objectives are to:

Determine the prevalence and yield of POC testing for CT, NG, TV, syphilis and hepatitis B, and factors associated with presence of STIs among pregnant women.Conduct a mixed-methods process evaluation to understand the acceptability and feasibility of POC STI testing and comprehensive case management in ANC settings.Estimate the cost and cost-effectiveness of integrated STI testing compared with standard of care.Investigate the prevalence of AMR for NG to inform the development of an EGASP in Zimbabwe.

## Methods and analysis

### Study design and setting

A prospective interventional study will be conducted in primary healthcare clinics (PHCs) in Harare province, Zimbabwe. The PHCs are all based in urban, high-density settings, and provide nurse-led services including ANC and uncomplicated deliveries. High-risk women receive their ANC at central hospitals, with referral also available if complications develop in labour. Opt-out HIV and syphilis testing using rapid diagnostic tests is part of routine care. GeneXpert devices are often available for tuberculosis diagnosis, but the study will provide an additional machine to ensure that sufficient diagnostic capacity is available. We previously demonstrated the feasibility of using non-laboratory technicians to operate the GeneXpert device for on-site CT/NG testing in community settings in Bulawayo, Zimbabwe.^29^

### Study population and recruitment

Pregnant women will be recruited when registering for routine ANC, starting in January 2023. It is the intention that only pregnant women attending their first ANC visit of this pregnancy will be recruited. However, if there is ongoing slower-than-expected recruitment, pregnant women attending for ANC follow-up visits will also be considered for enrolment. There will be no age cut-off for enrolment. Exclusion criteria will be enrolment in this study on a previous antenatal visit and being unable or unwilling to provide written informed consent. Recruitment will be conducted during weekdays only. Pregnant women will be consecutively enrolled as testing capacity allows.

Reasons for declining participation, and for exclusion, will be documented. If participants only consent to some of the STI tests, reasons for declining the others will be recorded.

### Study procedures

The full schedule of events for pregnant women is described in table 1. Following consent, an interviewer-administered questionnaire will collect sociodemographic data, clinical history including STI symptoms and recent antibiotic use, sexual and obstetric history. Contact information will be collected for follow-up.

**Table 1 T1:** Schedule of events for pregnant women

Participants	Activity	Day 0 (study entry)	Days 1–5	Days 4–14	On partner attendance	Birth	Post partum (planned telephone follow-up)
All	Informed consent	X					
All	Questionnaire	X					
All	HIV testing	X					
All	Syphilis testing	X					
All	HBV testing	X					
All	Vaginal swab collection	X					
All	CT/NG testing	X					
All	TV testing	X					
STI test positive	Health education	X					
HBV test positive	Venepuncture	X					
HBV test positive	HBV viral load and ALT testing	X					
HBV test positive	Referral to secondary care	X					
HIV test positive	Referral as per PHC processes	X					
CT/NG/TV/syphilis test positive	Provision of treatment	X					
CT/NG/TV/syphilis test positive	Partner notification advice and slip	X					
NG test positive	Cervical swab collection	X					
NG test positive	Plating of cervical swab and incubation at laboratory	X					
STI test positive Not treated on day 0	Contact participant by telephone and ask to return to PHC for treatment		X				
Cultured NG isolate	Storage of isolate at −80°C			X			
Partners	Provision of treatment to partners who attend PHC				X		
HBV test positive	Provision of HBV birth dose vaccine coordinated with PHC and secondary care					X	
CT/NG/TV/syphilis test positive	Contact by telephone to collect data on partner notification process						X
All	Contact by telephone to collect birth outcome data						X
All	Review of birth registry records to supplement birth outcome data from participants						X

ALT, alanine aminotransferase; CT, *Chlamydia trachomatis*; HBV, hepatitis B virus; NG, *Neisseria gonorrhoeae*; PHC, primary healthcare clinic; STI, sexually transmitted infection; TV, *Trichomonas vaginalis*.

Participants will provide three self-taken or provider-taken vaginal swab samples. One vaginal swab sample will be tested for CT and NG using the Xpert CT/NG assay (Cepheid), which has an analytical time of 90 min. The GeneXpert device will be operated using a rechargeable powerpack to provide an uninterrupted power supply. The second swab will be tested for TV using the OSOM Trichomonas Rapid Test (Sekisui Diagnostics), which has an analytical time of 10 min.^30^ The third swab will be stored for future studies including possible whole-genome sequencing. A fingerprick blood sample will be taken for HIV, syphilis and hepatitis B testing using the SD BIOLINE HIV/Syphilis Duo (Abbott Diagnostics Medical Co) (analytical time 20 min) and HBsAg 2 (Abbott Diagnostics Medical Co) (analytical time 30 min) rapid tests, respectively.^31^ HIV and syphilis testing, referral to HIV services, syphilis treatment and partner notification for those with HIV or syphilis are already part of routine care. The study team will work with health facility staff to integrate the additional STI testing with routine ANC services to prevent duplication of procedures.

Participants with positive test results and their partners will be managed in line with Zimbabwe national treatment guidelines.^32^ For participants with an STI syndrome on presentation, immediate treatment will be provided for syndromes such as pelvic inflammatory disease and genital ulcer disease, where testing will not alter management. For vaginal discharge syndrome, participants will ideally wait for their results to receive tailored treatment; however, they will receive metronidazole regardless of results, in order to cover for bacterial vaginosis. For symptomatic participants not willing or able to wait or return for their results, they will have the option to receive full syndromic treatment.

Participants will ideally collect their results and receive treatment if necessary within the same clinical visit. Participants who test positive for an STI but are unable to receive same-day treatment will be actively followed up by telephone, up to five times over a 28-day period, to advise them to return for treatment.

A client-referral approach will be used for notification of sexual partners. Women will be counselled on the importance of their partners receiving treatment and given partner notification (PN) slips for their partners to return for presumptive treatment. Although partners will be able to attend any clinic, treatment will be provided free of charge if they return to the study clinic.

Women newly diagnosed with HIV will be referred for antiretroviral therapy as per local PHC processes. Women newly diagnosed with hepatitis B will have hepatitis B viral load and alanine aminotransferase testing, alongside referral to a gastroenterology specialist in secondary care. Although hepatitis B vaccination is currently included in the Zimbabwe national vaccination schedule at 6, 10 and 14 weeks, birth dose vaccination is not yet standard of care in Zimbabwe. Birth dose vaccines will therefore be provided by the IPSAZ Study. This is likely to be logistically complex and bespoke strategies for implementation will be designed in conjunction with healthcare teams at the individual PHCs and with local secondary care providers.

Birth outcome data will be collected from birth registers, including birth weight, gestation, mode of delivery and stillbirth. Estimated due date, which will be compared with actual birth date to determine prematurity, will be based on last menstrual period. Participants will also be contacted by telephone post partum to facilitate this process by providing information on date and location of birth, and to provide supplemental data if necessary if the birth register is incomplete. Participants will also be asked about number of ANC visits, and for women with positive STI results, if they gave the PN slip to their partner, and if their partners were treated.

### Process evaluation

A mixed-methods process evaluation will be conducted, based on the Medical Research Council (MRC) Process Evaluation Framework.^33^ The focus will be on understanding what was implemented and how; how the intervention led to change; and how local context affects implementation and shapes outcomes. Linnan and Steckler’s process evaluation framework has also guided the choice of specific research domains related to implementation, where fidelity, dose and reach/coverage are central features.^34^

Table 2 details the process evaluation research domains and questions. A logic model demonstrating the proposed theory of change is shown in figure 1.

**Table 2 T2:** Framework for process evaluation

Framework domain	Research domain	Research questions	Data collection methods and sources
Implementation	Fidelity	How did implementation vary from the protocol that is (a) offering STI screening, (b) undertaking STI screening, (c) providing comprehensive case management including partner notification, (d) training and supervision of staff? What were the barriers and facilitators to implementation? What adaptations were made?	Routine monitoring data Structured observation FGDs with clinic staff (1–2 per PHC) and IDIs with research team (all members), pregnant women (8–10 per PHC), partners (3–4 per PHC) and clinic staff (4 per PHC)* IDIs with pregnant women who decline STI screening (3–4 per PHC) to explore reasons for this
	Coverage	What proportion of: (a) pregnant women attending antenatal care were offered STI screening, (b) pregnant women who were offered STI screening took it up, (c) positive STI cases were treated, (d) partners of positive cases were treated? How equitable was this coverage? What were the barriers and facilitators to each step?	
Mechanisms of impact	Responses to and interactions with the intervention	Which components of the intervention were best accepted and adopted by pregnant women and HCWs and why? What challenges and barriers were faced?	Structured observation FGDs and IDIs with pregnant women, partners and HCWs*
	Interactions and consequences	How did various components of the intervention interact? Were there any unanticipated pathways or consequences?	
Context	Proximal and distal	What social, cultural, political and logistical factors impede or facilitate how the intervention was implemented, and how were HCWs able to engage with and adopt aspects of the intervention? What were contextual reasons for adaptations to the intervention and its delivery?	FGDs and IDIs with pregnant women, partners and HCWs* Structured and unstructured observations Key informant interviews with local health authorities and community leaders Context diaries to record external events

*Number of IDIs/FGDs listed is approximation.

FGDs, focus group discussions; HCWs, healthcare workers; IDIs, in-depth interviews; PHC, primary healthcare clinic; STI, sexually transmitted infection.

**Figure 1 F1:**
[figure not shown]
Logic model for mixed-methods process evaluation. HBV, hepatitis B virus; HCW, healthcare worker; PHC, primary healthcare clinic; STIs, sexually transmitted infections.

Following initial qualitative formative work to refine the testing strategy, a concurrent triangulation strategy will be used, with quantitative and qualitative data collected in parallel, with similar weighting given to each.^35^ This will allow for triangulation of data in order to comprehensively address the process evaluation questions. Routine monitoring data will include uptake of testing, treatment and PN, as well as stock monitoring, debriefing minutes and recording of GeneXpert error codes. Data collection will also include structured and unstructured observation, and focus group discussions and in-depth interviews with key stakeholders including pregnant women, partners, clinic staff, policymakers and the research team involved in delivery of the intervention (including both the clinic-based team and laboratory staff). Different topic guides will be designed for interviews and focus group discussions at different stages of implementation, to reflect the changing focus of the process evaluation. Participants for interviews and group discussions will be purposively selected to ensure a relevant range of views for each stage of the process evaluation. Adaptations will be made to the testing strategy based on interim process evaluation findings to improve ongoing implementation.

Thematic analysis on qualitative data will be performed to identify and develop key themes and concepts on addressing what was implemented and how; how the intervention led to change; and how local context affects implementation and shapes outcomes.

### Economic evaluation

Cost-effectiveness will be evaluated as the ratio of incremental costs and incremental effects of POC testing for CT, NG and TV, in comparison with routine care using syndromic management. Total costs and effects will be estimated for each arm, with incremental values calculated from these estimates.

Clinical endpoints include mild infection, pelvic inflammatory disease, infertility and adverse birth outcomes including miscarriage, stillbirth, low birth weight and prematurity. Incidence of clinical endpoints will be estimated from existing literature, with such estimates for adverse birth outcomes being supported by primary data collection. Disability-adjusted life years will be the main outcome, and will be modelled based on clinical endpoints, predicted life expectancy and disability weights.^36^ Intermediate measures include cost per patient screened, diagnosed with an STI and treated. A simple static decision tree model will be used to structure the cost-effectiveness evaluation, which will be from a health system perspective.

Health system costs required to deliver the testing strategy will be collected from both primary and secondary data sources using a bespoke cost extraction tool. Financial and economic costs will be estimated based on study financial records, staff interviews, time-and-motion studies and other sources such as national salary scales for the Zimbabwe health service. Cost categories will include start-up costs such as training costs, capital costs including buildings and storage and equipment, and recurrent costs, including personnel, consumables, and transport costs. Costs associated with downstream complications of infection will be estimated from the literature. Costs incurred by patients while attending ANC, including transport costs and opportunity costs, will be collected using the interviewer-administered questionnaire. Additional costs associated with the testing strategy, such as a longer visit or to return for treatment, will be recorded.

Individual and combined parameter uncertainty will be investigated using deterministic and probabilistic sensitivity analyses. The cost-effectiveness of the testing strategy compared with syndromic management will be compared against appropriate cost-effectiveness thresholds for Zimbabwe.

### AMR surveillance

EGASP recommends the collection of at least 100 gonococcal isolates per year per country. Assuming a prevalence of NG of 3% among pregnant women, only 30 women with NG will be identified. To supplement the number of isolates obtained from ANC participants, men aged 18 years and above presenting with urethral discharge to the study clinics who provide written informed consent will be recruited. Consecutive sampling will be performed as resources allow, with the antenatal testing strategy taking priority.

Men with urethral discharge have been selected as the yield of a positive gonococcal culture will be high. Assuming an estimate of 50% NG prevalence among symptomatic men,^37^ we anticipate recruiting approximately 140 men with urethral discharge. We therefore estimate isolation of 70 gonococcal isolates from men which, in addition to 30 isolates from women, will give 100 NG isolates in total. If the prevalence of NG is lower than predicted, recruitment of men with urethral discharge will continue until 100 NG isolates have been obtained.

Data on age, sex, risk factors for STIs, including number of recent sexual partners and gender of sexual partners, current STI symptoms, recent antibiotic use, treatment provided at the PHC and previous STI diagnoses including HIV, will be collected using an interview-administered questionnaire. Nurse-collected urethral swabs will be collected from all enrolled men, and they will be managed syndromically according to national guidelines as part of routine care.

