### Testing procedures for AMR

WHO EGASP guidelines and standard operating procedures will be adapted for use with pregnant women, and otherwise followed for AMR testing for NG.^38^ Nurse-collected cervical samples will be obtained using ESwabs (COPAN Diagnostics) from women initially found to be positive for NG using the Xpert assay. Speculum examinations will be conducted by nurses with many years of experience performing these examinations, using plastic disposable speculums. Samples will be plated onto the InTray GC (Biomed Diagnostics) in-vitro device, as will urethral samples collected from men. These will be subsequently incubated in the laboratory and minimum inhibitory concentrations of ceftriaxone, cefixime, azithromycin and ciprofloxacin will be determined using Etest (bioMérieux) and interpreted using the European Committee on Antimicrobial Susceptibility Testing standards.^39^

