### Sample size calculations

There are limited data on STI prevalence in pregnant women in Zimbabwe. A prevalence of curable STIs between 32.0% and 37.0% has been reported in South Africa and Zambia.^12–16^ Our recent studies among female youth in Harare have demonstrated combined CT/NG prevalence between 18.2% and 19.5%.^18 19^ The prevalence of hepatitis B in pregnant women in South Africa has ranged between 3.1% and 5.3%.^20–22^ Therefore, a conservative estimate of composite prevalence of curable STIs and hepatitis B is 30.0%. With a desired precision of 3% and alpha of 0.05, a sample size of 896 is required. To allow for invalid test results, 1000 pregnant women will be screened. The minimum detectable ORs for factors associated with the presence of STIs at different composite prevalence of STIs are shown in table 3.

**Table 3 T3:** Minimum detectable ORs for factors associated with presence of STIs

Sample size*	STI prevalence	Precision	Smallest OR detected at 80% power	Smallest OR detected at 90% power
896	20%	2.6%	1.74	1.89
	25%	2.8%	1.67	1.80
	30%	3.0%	1.63	1.75

*Assuming a prevalence of a risk factor of 20% among those without STIs.

STIs, sexually transmitted infections.

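### The 100-isolate target for gonococcal resistance counts infected participants as isolates, and the rule for recruiting more men is triggered by low prevalence rather than by too few isolates

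*Protocol article*

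**What the plan says.** All references are to the protocol article.

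- **Target** (AMR surveillance): "EGASP recommends the collection of at least 100 gonococcal isolates per year per country".
- **Women** (AMR surveillance): "Assuming a prevalence of NG of 3% among pregnant women, only 30 women with NG will be identified". The 1000 comes from Sample size calculations: "To allow for invalid test results, 1000 pregnant women will be screened".
- **Men** (AMR surveillance): "Assuming an estimate of 50% NG prevalence among symptomatic men", "we anticipate recruiting approximately 140 men with urethral discharge". Every enrolled man has a urethral swab. The section expects a high culture yield in these men but gives no figure. Their recruitment depends on resources, and antenatal testing comes first.
- **Total** (AMR surveillance): "We therefore estimate isolation of 70 gonococcal isolates from men which, in addition to 30 isolates from women, will give 100 NG isolates in total".
- **Route to an isolate in women** (Testing procedures for AMR): "Nurse-collected cervical samples will be obtained using ESwabs (COPAN Diagnostics) from women initially found to be positive for NG using the Xpert assay". The sample is taken at a speculum examination, plated and incubated.
- **Continuation rule** (AMR surveillance): "If the prevalence of NG is lower than predicted, recruitment of men with urethral discharge will continue until 100 NG isolates have been obtained".

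**The concern.** Within one section, 30 women with infection become 30 isolates from women. The two are not the same quantity. The first is a count of positive molecular tests. The second requires that the woman then has a cervical swab taken and that the organism grows. No factor for either step appears. The men are treated alike: 50% prevalence in 140 men becomes 70 isolates.

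The continuation rule has a suitable end point, 100 isolates, but its condition is lower-than-predicted prevalence. Xpert prevalence in women could be exactly 3% while several cultures are missed or fail. Read literally, the condition would then not be met although isolates are short.

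AMR prevalence is a study objective and a listed outcome, and 100 isolates is the only basis given for its size. An understated number of men also matters for planning, because their recruitment is second in line for resources. The Discussion presents culture from pregnant women as something that could inform wider surveillance guidance, so the recovery expected in women is worth stating.

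**Working it through.** **Inputs from the article.** Women screened 1000; NG prevalence in women 0.03; men about 140; NG prevalence in men 0.50; target 100 isolates. Recovery is not given. Let r_w be the proportion of Xpert-positive women who yield an isolate (swab taken and culture grown), and r_m the proportion of infected men who do.

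**Formulas.**
- Expected isolates = 1000 × 0.03 × r_w + 140 × 0.50 × r_m = 30 r_w + 70 r_m
- Men needed for an expected 100 = (100 − 30 r_w) / (0.50 r_m), rounded up

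**Reproducing the plan.** With r_w = r_m = 1: 30 + 70 = 100, and men needed = (100 − 30)/0.50 = 140. The addition is correct. It holds only with r_w = 1 and with r_m = 1. If the 50% is already a culture-positive proportion, r_m = 1 is built in.

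**With recovery below 1.** The recovery values are assumptions.

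| r_w | r_m | Expected isolates | Men needed |
|---|---|---|---|
| 1.0 | 1.0 | 30 + 70 = 100 | 70/0.50 = 140 |
| 0.8 | 1.0 | 24 + 70 = 94 | 76/0.50 = 152 |
| 0.4 | 1.0 | 12 + 70 = 82 | 88/0.50 = 176 |
| 0.9 | 0.95 | 27 + 66.5 = 93.5 | 73/0.475 = 153.7, so 154 |
| 0.8 | 0.9 | 24 + 63 = 87 | 76/0.45 = 168.9, so 169 |

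The rows with r_m = 1 isolate the part of the point that does not depend on how the 50% was measured.

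**No slack.** Treating the two counts as independent binomials, the chance of at least 100 isolates from 1000 women and 140 men is about 52% at perfect recovery, 22% at 0.9/0.95 and 5% at 0.8/0.9 (women/men).

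**The trigger.** Observed prevalence in women is Xpert positives divided by women tested, and r_w does not enter it. A low r_w therefore lowers the isolate count and leaves the trigger unchanged. For men the sections describe swab and culture and mention no Xpert test, so a low r_m would probably appear as lower observed prevalence and would trigger the rule. The gap in the rule is thus mainly in women.

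**The case against.** Several stronger readings are tempting, and the article does not support them.

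- **That the plan will miss 100 isolates.** No recovery rate is given, 140 is approximate, and prevalence could exceed 3%. The Introduction cites NG up to 6.4% in pregnant women in the region. At 80% recovery, prevalence of 3%/0.8 = 3.75% would restore 30 isolates from women; at 40% it would take 3%/0.4 = 7.5%.
- **That recruitment stops at 140 men.** The 140 is a forecast. The only end point stated is 100 isolates, so the intention is sound and the gap is in the condition that starts continued recruitment.
- **That swab collection in men is a hidden assumption.** Swabs from all enrolled men are the stated procedure, and the 50% may already be culture-based. The cited source is not at hand.
- **That Table 1 rules out a cervical swab after day 0.** It marks the swab on day 0 only, but it marks treatment on day 0 only as well and still recalls untreated women later. Testing procedures for AMR sets no day limit.
- **That the loss falls mainly on women.** At 80% in women and 90% in men, women lose 6 isolates and men lose 7.

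It is also fair to say that 100 is a surveillance recommendation and not a powered sample size. For a resistance proportion of 50%, the approximate 95% half-width, 1.96 × √(0.25/n), is 9.8 percentage points at n = 100, 10.5 at 87 and 10.8 at 82, so the loss of precision is modest.

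These objections limit the point but do not remove it. The article still equates Xpert-positive women with isolates, and the trigger still does not respond to lost cultures in women.

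**Conclusion.** The point holds in a limited form. The expected 100 isolates rests on an unstated recovery of 100%: clearly so in women, where a further swab and a culture lie between the positive result and an isolate, and in men unless the 50% is culture-based. The continuation rule, as worded, does not cover lost or failed cultures in women.

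With men at 100% and women at 40–80%, the stated numbers give 82–94 isolates, and about 152–176 men would be needed. With women at 80% and men at 90%, they give 87 isolates and about 169 men. These sizes rest on assumed recoveries together with the article's own 3% and 50%. That any recovery below 100% puts the expected total under 100 at the stated numbers does not depend on which values are assumed.

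**What to change.** In the AMR surveillance section:

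1. Describe 30 and 70 as expected infected participants, not isolates.
2. State an assumed recovery proportion for women (swab obtained and culture grown), and for men too if the 50% is not culture-based. Say which kind of figure the 50% is.
3. Restate the expected isolates and the indicative number of men from those assumptions.
4. Reword the continuation rule so that its condition is the isolate count: recruitment of men continues until 100 isolates are obtained, whatever the reason for the shortfall.

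The cost is a few sentences and one restated figure. The indicative number of men rises, with the staff time and culture supplies that go with it, but this stays within the plan's existing commitment to 100 isolates.
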